## 7 ASSESSMENTS

These are outlined in the schedule (Appendix 1). Further details are given below.

### 7.1 Clinical evaluations

#### 7.1.1 History, symptoms & examination

These will follow a standard format and data will be entered onto the case record form (CRF). The symptom checklist will be readministered on Days 3, 7, 14 etc to D42. Vital signs (pulse, blood pressure, respiratory rate and temperature) will be recorded 12 hourly in hospital and done at each outpatient visit. The aural or axillary temperature will be taken.

Body weight will be recorded at screening to the nearest kilogram using a suitable weighing scale. The scales will be properly calibrated.

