### 3.10.2 Primaquine/placebo administration

PQ/placebo dosing will be based on age. There will be four blister packs labelled A, B, C and D for the four age groups (see Section 5.3). Blisters A and B will contain 2.5 mg of PQ/placebo and C and D will contain 5 and 7.5 mg of PQ/placebo, respectively.

The PQ/placebo blister packs will be labelled sequentially to match the randomisation sequence for that age dosing band and will be allocated to patients in numerical order. Therefore, each patient will have a unique drug number as well as a unique subject number.

An example of the numbering is shown below for age band A, G6PDd: A-D-001

[figure not shown]

The running number is 001 for the first patient, 002 for the second patient etc. We will discuss the drug packaging and randomisation system with Bilcare (the packaging company) and then decide on/fine tune the final labelling and randomisation scheme.

The allocation of AL or DHAPP and PQ/placebo will be organised at each site in order to minimise the chances of an error in drug allocation. Accordingly, a detailed Randomisation / Drug management guideline will be written.

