## 5 STUDY DRUGS

### 5.1 Artemether lumefantrine

AL is the recommended first line drug for falciparum malaria in DRC and Uganda.

GMP manufactured AL will be obtained from a reliable manufacturer or official supplier either locally or externally and imported. If imported all necessary documentation will be obtained (e.g. certificate of analysis, etc). AL will be dosed by weight, in accordance with the manufacturer's recommendation. One tablet of dispersible and non-dispersible AL contains 20 mg of artemether and 120 mg of lumefantrine.

AL is dose twice daily. On the first day of treatment the doses are separated by 8 hours but by 12h on the second and third days of treatment. The total course is 6 doses.

| Weight in kg | Number of tablets / dose | Total number of tablets / day | Total number of tablets / course |
|--------------|--------------------------|-------------------------------|----------------------------------|
| 5 - <15      | 1                        | 2                             | 6                                |
| 15 - < 25    | 2                        | 4                             | 12                               |
| 25 - < 35    | 3                        | 6                             | 18                               |
| ≥ 35         | 4                        | 8                             | 24                               |

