### 5.2 Dihydroartemisinin piperazine

DHAPP has been extensively used in Africa and Asia and the Sigma Tau formulation is registered in several African countries and was registered in the European Union in 2011.

GMP produced DHAPP will be obtained from a reliable source and, if imported, all necessary documentation will be obtained. DHAPP will be dosed by weight. The 2015 WHO guidelines now recommend a dose of  $\geq 2.5$  mg/kg/day of DHA in children who weigh  $< 25$  kg (<http://www.who.int/malaria/publications/atoz/9789241549127/en/>).

There are three DHAPP tablet strengths, all in mgs:

- DHA 20 PP 160
- DHA 40 PP 320
- DHA 80 PP 640

The teams will modify the WHO dosing chart according to the tablet strengths they are able to obtain in Kinshasa and Uganda.

Table 1. DHAPP dosing table from the WHO.

| Body weight (kg) | Dihydroartemisinin + piperaquine dose (mg) given daily for 3 days |
|------------------|-------------------------------------------------------------------|
| 5 to < 8         | 20 + 160                                                          |
| 8 to < 11        | 30 + 240                                                          |
| 11 to < 17       | 40 + 320                                                          |
| 17 to < 25       | 60 + 480                                                          |
| 25 to < 36       | 80 + 640                                                          |
| 36 to < 60       | 120 + 960                                                         |
| 60 < 80          | 160 + 1280                                                        |
| >80              | 200 + 1600                                                        |

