### 5.3 Primaquine/placebo

PQ/placebo (2.5, 5, 7.5 mg PQ base) will be manufactured for this trial by Centurion Remedies, PVT Ltd, Gorwa, India. This is a WHO certified manufacturing facility. Bilcare Ltd, Pune, India, will blister pack the PQ/placebo and will manage their export from India to the DRC and Uganda, in accordance with all applicable drug regulations.

Bilcare Ltd has already supplied quality, GMP manufactured PQ/placebo for MORU for another large trial (NCT01814683). The batch of PQ/placebo used for this trial will be quality controlled and a certificate of analysis will be supplied by Bilcare Ltd.

Dosing will be by age. The target dose of PQ is 0.25 mg/kg with a therapeutic dosing range of 0.15 - 0.4 mg/kg given once with the first dose of AL or DHAPP. Children will receive doses ranging from 0.1 - 0.46 mg/kg. A detailed breakdown of the mg/kg dose that a child will receive is shown in Table 2.

For young children who cannot swallow, the PQ/placebo tablet will be dissolved in 5 mL of sugar water (or similar solution depending on local practice) and the dose administered. The 2.5 mg PQ/placebo tablet will be used for children aged 6-11m but they will be given 2.5 mL of suspension and so will receive 1.25 mg of PQ/placebo. Guidelines on the practicalities of drug administration will be written.

Table 2. Dosing table by age of PQ showing the mg/kg dose received.

| Age   | Primaquine dose in mg base | minimum | 1 st quartile | median | 3 rd quartile | Maximum |
|-------|----------------------------|---------|--------------------------|--------|--------------------------|---------|
| 6-11m | 1.25                       | 0.1     | 0.15                     | 0.16   | 0.18                     | 0.3     |
| 1y    | 2.5                        | 0.16    | 0.25                     | 0.27   | 0.3                      | 0.46    |
| 2y    | 2.5                        | 0.14    | 0.2                      | 0.22   | 0.25                     | 0.37    |
| 3y    | 2.5                        | 0.12    | 0.17                     | 0.19   | 0.21                     | 0.32    |
| 4y    | 2.5                        | 0.11    | 0.16                     | 0.17   | 0.19                     | 0.29    |
| 5y    | 2.5                        | 0.1     | 0.15                     | 0.16   | 0.18                     | 0.25    |

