## 7.2 Primaquine, lumefantrine and piperaquine concentrations

There are no PQ/cPQ PK data in children <5 years so data from this trial will be crucial to determine whether the age based regimen in this study is suitable for children in this age group and allow us to compare PQ and cPQ exposures as a function of age and the ACT given.

The pharmacokinetics of PQ and cPQ will be characterised by non-compartmental analysis from blood samples at fixed time points. PK sampling will be done in Kinshasa and Uganda. The number of patients who will be sampled at each site will be 300:

- AL treated children aged < 5y (n=100)
- AL treated children aged 5-11 years (n=50)
- DHAPP treated children aged < 5y (n=100)
- DHAPP treated children aged 5-11 years (n=50)

Therefore, a total of 600 patients will be sampled. Approximately half will have received PQ and the other half placebo. Thus, the total number of patients with PQ PK data will be 300. We will keep a tally of patient numbers and once the required number of patients has been sampled we will stop the PK. Given the relative lack of children aged 5-11 years, we may not reach the sample size for this group.

For those children who received placebo, we will analyse the lumefantrine and piperaquine concentrations in the first 24 hours. We will insert an intravenous catheter at enrolment in children that will remain in place for 24 hours and draw up to a maximum of 8 samples per child (less if demanded by the local ethics committees) at fixed time points. Given the uncertainty of the outcome of the ethical review, we will select eight time points from this schedule: 0, 1, 1.5, 2, 3, 4, 6, 8, 10, 12, 24h.

Participation in this PQ PK sampling regimen is optional in Uganda but is considered part of the study in Kinshasa.

A venous blood sample for lumefantrine and piperaquine concentrations will be taken on D0, D3, D7, and D28

The sample size for lumefantrine is 200 – ~100 who will receive PQ and ~100 who will receive placebo. The sample size for piperaquine is also 200 with a 50-50 PQ-placebo split.

Comparing the D7 concentrations of both drugs between the PQ and placebo arms will determine whether PQ has affected their dispositions. Both lumefantrine and piperaquine D7 concentrations are valuable predictors of treatment failure in *P. falciparum*.

All PK samples will be analysed at the MORU PK laboratory in Thailand using MCMS / MS.

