## 11.2 Analyses & analysis populations

All patients who received at least one dose of ACT and PQ/placebo will be included in the analysis. All analyses will be detailed later in a prospectively written analysis plan. Below is a summary.

The main strategy for analysis of the primary end point will be assessed by chi squared or Fisher's exact test, as appropriate, calculating the 95% CIs of the risk difference to see if ACT + SLDPQ has achieved non-inferiority in the G6PDd group. Logistic regression will be used to adjust for potential confounders. Non inferiority will be assessed on the whole data set i.e. combining data from both sites using the lower end of the 95% confidence interval. Other proportional data will also be analysed by chi squared or Fisher's exact test.

Continuous data (e.g. Hb, biochemistry, parasite counts) between two groups will be analysed by the unpaired 't' test, transforming the data, as needed.

All analyses will be two sided and a p value of < 0.05 is considered statistically significant.

We will examine factors that are associated with: (i) the development of profound / severe anaemia (logistic regression), (ii) parameters of Hb recovery (multiple regression). *A priori*, we will explore the relationships between Hb profiles in the following: (i) G6PD status (defined by genotype and by enzyme activity), (ii) any IBD vs. not, (iii) age <5 vs. age ≥5y, (iv) high biomass infections, assessed by microscopy and measured HRP2 concentrations, and (v) males vs. females. For these analyses, estimates and 95% confidence intervals (CIs) will be presented but not p values.

The PK data for PQ and cPQ will be analysed by non-compartmental analysis. The following PK parameters will be estimated:

- Cmax
- Tmax
- Clearance
- Half life
- AUC
- Vd

For lumefantrine and piperaquine, drug absorption kinetics will be modelled over the first 24 hours.

The Day 7 concentrations of lumefantrine and piperaquine will be compared between PQ and placebo recipients. Depending on the lumefantrine and piperaquine data obtained, other modelled PK parameters will be determined, as the data permit.

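### Minor: weight is recorded once, to the nearest kilogram, which is too coarse for mg/kg values in infants and for ACT dose bands that open on whole kilograms

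*Protocol*

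**What the plan says.** Section 7.1.1 of the protocol: "Body weight will be recorded at screening to the nearest kilogram using a suitable weighing scale". Appendix 1 has one mark in the weight row, at enrolment. The body of Appendix 2 (Uganda outpatients) is blank in the copy I have, so I cannot check that schedule, but section 7.1.1 specifies only the screening weight.

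Weight is used in three places.

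- **ACT dose.** Section 5.1: "AL will be dosed by weight", with bands opening at 5, 15, 25 and 35 kg. Section 5.2: "DHAPP will be dosed by weight". Within the trial's likely weights, Table 1 changes dose at 8, 11, 17, 25 and 36 kg. That table is provisional: "The teams will modify the WHO dosing chart according to the tablet strengths they are able to obtain in Kinshasa and Uganda".
- **Primaquine in mg/kg.** Section 3.10.2: "PQ/placebo dosing will be based on age". The dose is nevertheless described per kilogram. Section 5.3 gives a therapeutic range of 0.15-0.4 mg/kg and says "Children will receive doses ranging from 0.1 - 0.46 mg/kg".
- **PK.** Section 7.2 calls the data in children under five "crucial to determine whether the age based regimen in this study is suitable for children in this age group". Section 11.2: "The PK data for PQ and cPQ will be analysed by non-compartmental analysis", and its parameter list includes clearance and volume of distribution.

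No section gives a finer weight or a rule for a child who rounds onto a band edge.

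**The concern.** Rounding to 1 kg costs little in a 25 kg child and noticeably more in a 7 kg infant. The mg/kg error is therefore largest in the ages where the trial wants to learn whether age-based primaquine dosing is right. Precision not written on the CRF cannot be recovered later by any analysis plan.

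The second issue is one-sided. Because the bands open on whole kilograms, rounding to the nearest kilogram can move a child up into the next band but never down. A child of 14.5-14.9 kg becomes 15 kg and receives two AL tablets per dose instead of one. This happens only if the recorded value selects the band, which the protocol leaves open. Section 4.5 classes a wrong dose of study drug as a protocol violation, so an explicit rule is worth having.

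**Working it through.** The protocol states no figure for this point, so there is none to reproduce first.

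**Weights by age.** From Table 2, median weight = dose / median mg/kg, and log SD = ln(Q3/Q1)/1.349. I assume weight is lognormal within each year of age.

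- 6-11 months: 1.25/0.16 = 7.81 kg; ln(0.18/0.15)/1.349 = 0.135
- 1 year: 2.5/0.27 = 9.26 kg; log SD 0.135
- 2 years: 2.5/0.22 = 11.36 kg; log SD 0.165
- 3 years: 2.5/0.19 = 13.16 kg; log SD 0.157
- 4 years: 2.5/0.17 = 14.71 kg; log SD 0.127

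**Rounding error in mg/kg.** Error = (dose/recorded weight)/(dose/true weight) - 1 = true/recorded - 1, rounding half up. Simulated with 2 million draws per age:

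| Age | RMS, 1 kg | Error above 5%, 1 kg | RMS, 0.1 kg |
|---|---|---|---|
| 6-11 m | 3.78% | 21.2% | 0.38% |
| 1 y | 3.18% | 9.1% | 0.32% |
| 2 y | 2.62% | 2.0% | 0.26% |
| 3 y | 2.25% | 0.3% | 0.22% |
| 4 y | 2.00% | 0% | 0.20% |

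A hand check agrees: (1/√12)/7.81 = 3.7% at the infant median. The mean error is 0.14% in infants and 0.04% at 4 years, so group means are essentially unbiased. Table 2 is itself rounded to two decimals. Allowing for that, the infant RMS is 3.6-4.0% and the share above 5% is 18-24%. At 0.1 kg the worst case is 0.05/4.17 = 1.2%, at the lowest infant weight Table 2 implies (1.25/0.3 = 4.17 kg).

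**One effect that does not average out.** An infant given 1.25 mg is below 0.15 mg/kg when heavier than 1.25/0.15 = 8.33 kg. Infants of 8.33-8.5 kg are recorded as 8 kg, which gives 1.25/8 = 0.156 mg/kg, inside the range. Under the same model 31.6% of infants are truly below 0.15 mg/kg but only 26.6% appear so. With 0.1 kg recording about 0.5% are misclassified. The shares depend on Table 2's rounded quartiles; the direction does not.

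**Band edges, if the recorded weight chooses the band.** Probability of lying within 0.5 kg below a cut:

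| Age | AL (15, 25, 35 kg) | DHAPP as printed (8, 11, 17, 25, 36 kg) |
|---|---|---|
| 6-11 m | 0% | 19.7% |
| 1 y | 0% | 15.5% |
| 2 y | 2.4% | 12.1% |
| 3 y | 6.6% | 7.5% |
| 4 y | 10.6% | 6.3% |

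The protocol gives no age mix. Assumed weights 0.5:1:1:1:1 give:

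- AL: (0 + 0 + 2.4 + 6.6 + 10.6)/4.5 = 4.4%
- DHAPP: (0.5×19.7 + 15.5 + 12.1 + 7.5 + 6.3)/4.5 = 11.4%

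Three other assumed mixes give AL 3.2-5.1% and DHAPP 10.4-12.5%. Letting the Table 2 values vary within their rounding gives AL 3.5-5.7% and DHAPP 10.0-12.7%. At 5-11 years AL is 2.8-9.1% by year of age, mean 5.4% with equal ages. Section 7.2 plans 100 AL-treated under-fives for PK at each of two sites, so 200 × 4.4% ≈ 9 children (200 × 3.2% ≈ 6 to 200 × 5.1% ≈ 10).

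**Size of the resulting doses.**

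- AL, artemether per dose at 14.5 kg: 20/14.5 = 1.38 mg/kg correctly banded, 40/14.5 = 2.76 if moved up. The upper band's own maximum is 40/15 = 2.67, so the excess is 3.4%.
- DHAPP, DHA at 7.5 kg: 20/7.5 = 2.67 mg/kg correctly banded, 30/7.5 = 4.00 if moved up. The upper band's own maximum is 30/8 = 3.75, so the excess is 6.7%.
- Both schedules already give 20/5 = 4.0 mg/kg at 5 kg. No moved-up child exceeds that.

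**The case against.** The strongest reply is that little in the plan depends on this weight. Cmax, Tmax, half-life and unscaled AUC do not use it, and section 11.2 does not say that clearance or volume will be divided by weight. Section 7.2 compares exposures by age and ACT. In infants the true and recorded mg/kg values correlate at 0.96, and rounding inflates the log SD by only 3.9%. With the minimum of 80 infants in section 3.10.3 and about half on primaquine, 21% is roughly 8 children. All of this stands and limits the finding. It does not remove it, because the protocol sets its primaquine range in mg/kg, so actual doses have to be compared with that range using these weights.

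On the bands, section 7.1.1 says how weight is recorded, not which value selects the dose. A 14.7 kg child is plainly below 15 kg, and drug-handling guidelines not yet written may settle the matter. That is right, so the band figures are conditional. The DHAPP figure needs the further condition that Table 1 is used unmodified, which section 5.2 says will not generally be so.

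Finer weights also have a cost at two DHAPP edges, where rounding up would have raised the dose. Children of 16.5-16.9 and 24.5-24.9 kg would stay at 40/16.9 = 2.37 to 60/24.5 = 2.45 mg/kg DHA, just under the 2.5 mg/kg that section 5.2 cites for children below 25 kg. That is a property of the printed bands, and the sites' modified charts may change it.

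Finally, the protocol does not give the resolution of the sites' scales, so the low cost is an assumption.

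**Conclusion.** The point holds as a minor one. Whole-kilogram recording puts an avoidable error on individual mg/kg and per-kg values, about 3.8% RMS in infants and falling with age, and understates the share of infants below 0.15 mg/kg by about 5 percentage points. If the recorded weight also selects the ACT band, about 4% of under-fives on AL are given the next band's dose, and about 11% on DHAPP if the printed chart is used.

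The randomised primaquine dose, the primary comparison, the sample size and group means are not affected, and no dose goes above what the schedules already allow. The sizes rest on lognormal weights read back from Table 2 and, for the band figures, on assumed age mixes.

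**What to change.** In section 7.1.1, record weight to 0.1 kg. State that this value, without further rounding, selects the AL or DHAPP band and is used in every mg/kg and per-kg calculation. No band, dose or sample size changes. The cost is one decimal on the CRF and a scale reading to 0.1 kg at each site, which should be confirmed. When the sites adapt the DHAPP chart to their tablet strengths, they should look at children just below 17 and 25 kg, who fall slightly short of 2.5 mg/kg DHA under the printed bands.

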#### 7.1.2 Reading malaria blood films

Blood films will be prepared at baseline, 6 and 12 hours and then every 12 hours until 2 consecutive negative blood films are observed (inpatients only).

Asexual and sexual parasites will be identified and counted by microscopy (magnification of 1000×) on Giemsa-stained thin and thick films.

Parasitaemia will be measured on a thin blood film if more than 200 parasites per 10 fields on a thick film are seen: 2000 RBCs will be read and the number of parasitised infected RBCs noted.

Below this threshold, the parasitaemia will be counted per 500 WBC on the thick film.

Slides are considered negative after examination of at least 200 high-power microscopy fields.

The final parasitaemia is calculated as follows:

- Thin film:  $N \text{ parasites} / 2000 \text{ red blood cell on the thin smear} \times \text{Hct} \times 125.6$

2

- Thick film: N parasites/500 white blood cells on the thick smear x 16

Slides will be cross checked blinded by the research team, as follows:

- 10% of all D0 slides
- all positive slides on D3 and D7
- 10% of negative slides on D3 to D28.

Two qualified microscopists will read all the slides independently. Blood smears with discordant results:

- different parasite species
- a difference in parasite density of > 50%
- positive/negative slide

will be re-examined by a third, independent microscopist, and parasite density will be calculated by averaging the two closest counts.

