#### 3.4 Secondary endpoints

The secondary endpoints are to determine/measure/assess:

- Haemoglobin concentrations over time:
  - Fractional change in haemoglobin on Day 7 vs. baseline
  - Proportion of patients with a fractional change  $\geq 25\%$
  - Time to nadir Hb concentration
- Determinants of changes in Hb concentration over time
- G6PD genotype (hemizygous male, homo-, heterozygous female, normal and selected G6PD variants e.g. G6PD A- 202 mutation)
- G6PD enzyme activity

- Genotypes of other inherited blood disorders
- Incidence of adverse events
- Pharmacokinetic characteristics of PQ, carboxyPQ, lumefantrine and piperaquine
- CYP 2D6 genotypes
- Asexual parasitaemia clearance time and half life
- Therapeutic efficacy of AL and DHAPP using the WHO criteria (Appendix 3)
- Gametocytaemia over time
- Proportion of patients with gametocytes over time

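### Just above the switch from thick to thin film, the fixed 2000-red-cell count rests on roughly 4–11 parasites, so densities there are avoidably imprecise and the 50% discordance check often fires by chance

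*Protocol*

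**What the plan says.** Protocol Section 7.1.2 sets the rule for choosing the film: "Parasitaemia will be measured on a thin blood film if more than 200 parasites per 10 fields on a thick film are seen". On the thin film, "2000 RBCs will be read and the number of parasitised infected RBCs noted". The conversion multiplies by haematocrit and 125.6. Otherwise, "Below this threshold, the parasitaemia will be counted per 500 WBC on the thick film", converted as "Thick film: N parasites/500 white blood cells on the thick smear x 16". No minimum number of parasites is required on either film.

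Quality control is by double reading: "Two qualified microscopists will read all the slides independently". One trigger for a further reading is "a difference in parasite density of > 50" per cent; the section does not say of what. Such slides "will be re-examined by a third, independent microscopist, and parasite density will be calculated by averaging the two closest counts".

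Section 3.4 lists "Asexual parasitaemia clearance time and half life" among the secondary endpoints.

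**The concern.** The relative error of a count depends on the number of parasites counted, not on the density. The rule leaves a film that samples many parasites for one that samples few at the point where the thin film has least to count. If only a handful of parasites is expected among 2000 red cells, a slide just above the switch gets a far noisier density than one just below it.

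Two things are at stake. First, inpatient films are taken at 0, 6 and 12 hours and then 12-hourly, so a falling parasite curve can start on the imprecise method and pass to the precise one partway, which adds noise to clearance time and half-life. Second, a 50% limit applied to very small counts sends correctly read slides to a third microscopist because of sampling variation alone.

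**Working it through.** The protocol states no expected count, CV or discordance rate, so there is no figure to reproduce. The check uses its conversion rules plus two assumptions.

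**Inputs from Section 7.1.2**
- Switch: more than 200 parasites per 10 fields, i.e. 20 per field.
- Thick film: 500 white cells, factor 16. This implies 16 × 500 = 8,000 white cells/µL.
- Thin film: 2000 red cells. The 2 that stands apart from the formula is read as its divisor, so density = (N/2) × Hct × 125.6. This is plausible: at Hct 40, 40 × 125.6 × 1000 = 5.02 million red cells/µL, so Hct × 125.6 is the factor per 1000 red cells and must be halved for 2000.

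**Assumptions (not in the protocol)**
- White cells per thick-film field, w: 8 to 20.
- Haematocrit: 30%, with a range of 20–36%.

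**Value of one counted parasite.** Thin film at Hct 30: 30 × 125.6 / 2 = 1,884/µL. Thick film: 16/µL. The thin-film unit is 1,884/16 = 118 times coarser, so its Poisson CV is √118 ≈ 11 times larger on the same slide. This ratio does not depend on w. It is √(1,256/16) ≈ 9 at Hct 20 and √(2,261/16) ≈ 12 at Hct 36.

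**At the switch.** Density = (20/w) × 8,000. Expected thin-film count N = density/1,884. CV = 1/√N, divided by √2 for the mean of two readers. Expected thick-film count = density/16. Chance discordance is the exact sum over two independent Poisson counts a and b with |a − b| above 50% of the lower count, the mean or the higher count. At Hct 30:

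| w | Density/µL | Thin N | CV, one reading | CV, mean of two | Thick N | Thick CV | Discordant by chance (lower / mean / higher) |
|---|---|---|---|---|---|---|---|
| 8 | 20,000 | 10.6 | 31% | 22% | 1,250 | 2.8% | 34% / 25% / 12% |
| 16 | 10,000 | 5.3 | 43% | 31% | 625 | 4.0% | 49% / 41% / 25% |
| 20 | 8,000 | 4.2 | 49% | 34% | 500 | 4.5% | 53% / 46% / 30% |

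The extremes over both assumptions are:
- w = 8, Hct 20: N = 15.9, CV 25%, discordance 25% / 16% / 6%.
- w = 20, Hct 36: N = 3.5, CV 53%, discordance 56% / 50% / 33%.

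**Further above the switch (Hct 30)**

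| Density/µL | Thin N | CV, one reading | Discordant by chance (lower / mean / higher) |
|---|---|---|---|
| 50,000 | 26.5 | 19% | 14% / 7% / 1% |
| 100,000 | 53 | 14% | 4% / 1% / 0.1% |
| 200,000 | 106 | 10% | below 0.5% on any base |

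**The case against.** The strongest reply is that this is a narrow band with safeguards already in place. Every slide has two independent readings, which takes a CV of 43% to about 31%. A third reading is triggered where counts are sparse and adds information there. Half-life is fitted to serial films, and later films below the threshold use the more precise count. All of this stands. It reduces the noise but leaves the band far less precise than the thick film would be.

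The 3–5% for the thick film is also only a floor. The 500 white cells are themselves a count (1/√500 = 4.5%), and reading error comes on top. The elevenfold ratio therefore compares parasite-counting error only. Adding the white-cell term in the middle case gives √(4.0² + 4.5²) ≈ 6%, still well below 43%.

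Three stronger readings are tempting, and the documents do not support them:
- That high densities in general carry a CV near 40%. They do not: it is 19% at 50,000/µL and 14% at 100,000/µL.
- That a large share of all the trial's slides will be discordant. The protocol gives no density distribution, so the share of slides near the switch is unknown.
- That the Day 2 and Day 3 failure rules in Appendix 3, or the high-biomass factor in Section 11.2, are compromised. No misclassification rate has been worked out, and high biomass is also assessed by HRP2.

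Nor does the fixed factor 16 put the two films on different scales. Both formulas estimate parasites per µL, and no bias between them has been shown.

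**Conclusion.** The point holds as a limited one. Just above the switch, at about 8,000–20,000/µL if a thick-film field holds 8–20 white cells, the 2000-red-cell count rests on roughly 4–11 parasites at Hct 30 (3.5–16 over Hct 20–36). One reading has a CV of about 30–50%, and the mean of two about 22–34%. In that band 12–53% of perfect reader pairs at Hct 30 breach the 50% limit by chance, so the check there largely detects sampling variation. The width of that range comes partly from the undefined base of the percentage.

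The conclusion rests on the assumed white cells per field and haematocrit, on reading the detached 2 as a divisor, and on Poisson counting. The loss of precision at the switch does not depend on the first of these. The consequence is confined to parasite density and clearance. The primary endpoint in Section 3.3 is defined by haemoglobin and clinical features and is not affected. This is a cheap improvement, not a flaw that threatens the trial.

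**What to change.** - Set a minimum number of parasites for a thin-film result, for example 20 (CV 1/√20 = 22%). If 2000 red cells yield fewer, either use the 500-white-cell thick-film count for that slide, or keep reading until the minimum is reached and put the red cells actually read into the formula. Choose one option for both sites. Replacing only low thin-film counts leaves a slight upward bias near the minimum.
- State whether the 50% is of the lower count, the mean or the higher count.
- Where a full blood count exists for that day, use measured white cells/500 in place of 16. Keep 16 only where there is none. Section 7.1.5 schedules counts on Days 0, 3, 7 and 28, but Section 3.8 makes enrolment testing depend on a suitable machine and Section 3.10.7 allows Hb and haematocrit instead.

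The cost is reading time just above the switch. At Hct 30, reaching 20 parasites needs on average 20 × 3,768,000/10,000 ≈ 7,500 red cells at 10,000/µL and about 3,800 at 20,000/µL. Above about 37,700/µL (20 × 1,884) 2000 cells suffice on average. Fewer chance referrals to the third reader offset part of this. The other drawback is some mixing of measured and assumed white cell counts where the blood count is missing, so the source should be recorded with each density.
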